**Table 4: Schedule of Assessments – Part D**

| Study Procedures                    | Screening
(Days -35 to -2) | Day
-1 | Days 1 to 12                                                                                                                                                                                                                                                                                                                                                                                                                                                                                                                                                                           | Days 13
and 14        | Early
Termination | Follow-up
(Day 15) |
|-------------------------------------|-------------------------------|-----------|----------------------------------------------------------------------------------------------------------------------------------------------------------------------------------------------------------------------------------------------------------------------------------------------------------------------------------------------------------------------------------------------------------------------------------------------------------------------------------------------------------------------------------------------------------------------------------------|--------------------------|----------------------|-----------------------|
| Pharmacokinetics:            |                               |           |                                                                                                                                                                                                                                                                                                                                                                                                                                                                                                                                                                                        |                          |                      |                       |
| Blood sampling                      |                               |           | 
Group D1:
Day 1: Prior to first dose and 0.25, 0.5, 1, 2, 3, 4, 6, 8, 10, and 12 hours post first dose (12-hour sample will be prior to second dose)
Days 2 to 9: Prior to first dose
Day 10: Predose and 0.25, 0.5, 1, 2, 3, 4, 6, 8, 10, 12, 24, 36, and 48 hours postdose
 
Group D2:
Day 1: Prior to first dose and 0.25, 0.5, 1, 2, 3, 4, 6, and 8 hours post first dose (8-hour sample will be prior to second dose)
Days 3 to 9: Prior to first dose
Day 10: Predose and 0.25, 0.5, 1, 2, 3, 4, 6, 8, 10, 12, 24, 36, and 48 hours postdose
 | 72 and 96 hours postdose | X                    | 120 hours postdose    |
| Pharmacodynamics:            |                               |           |                                                                                                                                                                                                                                                                                                                                                                                                                                                                                                                                                                                        |                          |                      |                       |
| Blood for biomarkers e   |                               |           | 
Day 1: Prior to first dose and 0.5 and 2 hours post first dose
Day 10: Predose and 0.5 and 2 hours postdose
                                                                                                                                                                                                                                                                                                                                                                                                                                                                 |                          | X                    | X                     |
| Blood for metabolomics f |                               |           | 
Day 1: Prior to first dose and 0.5 and 2 hours post first dose
Day 10: Predose and 0.5 and 2 hours postdose
                                                                                                                                                                                                                                                                                                                                                                                                                                                                 |                          | X                    | X                     |
| Safety and tolerability:     |                               |           |                                                                                                                                                                                                                                                                                                                                                                                                                                                                                                                                                                                        |                          |                      |                       |
| Adverse event recording             | X                             | X         | Ongoing                                                                                                                                                                                                                                                                                                                                                                                                                                                                                                                                                                                | X                        | X                    | X                     |

**Table 4: Schedule of Assessments – Part D**

| Study Procedures                                                                         | Screening
(Days -35 to -2) | Day
-1      | Days 1 to 12                                                                                                                                                                                         | Days 13
and 14 | Early
Termination | Follow-up
(Day 15) |
|------------------------------------------------------------------------------------------|-------------------------------|----------------|------------------------------------------------------------------------------------------------------------------------------------------------------------------------------------------------------|-------------------|----------------------|-----------------------|
| Prior/concomitant medication monitoring                                                  | X                             | X              | Ongoing                                                                                                                                                                                              | X                 | X                    | X                     |
| Clinical laboratory evaluations g                                             | X                             | X              | Day 7: Prior to first dose
Day 10: Predose and 48 hours postdose                                                                                                                                  |                   | X                    | X                     |
| C-reactive protein, erythrocyte sedimentation rate, and faecal calprotectin h |                               | X              | Day 4: Prior to first dose
Day 10: Predose                                                                                                                                                        |                   |                      | X                     |
| Blood pressure, pulse rate, and body temperature i                            | X                             | X              | Day 1: Prior to first dose and 2, 4, and 12 hours post first dose (12-hour sample will be prior to second dose in Group D1)
Days 2 to 9: Prior to first dose
Day 10: Predose
Days 11 and 12 | X                 | X                    | X                     |
| Safety 12-lead ECG                                                                       | X                             | X j | Day 1: 2 hours post first dose
Days 2 to 9: Prior to first dose
Day 10: Predose
Days 11 and 12                                                                                              |                   | X                    | X                     |
| Complete physical examination                                                            | X k                |                |                                                                                                                                                                                                      |                   | X                    | X                     |
| Symptom-directed physical examination                                                    |                               |                | Days 1 to 9: Prior to first dose
Day 10: Predose
Days 11 and 12                                                                                                                                |                   |                      |                       |

Abbreviations: BID = twice daily; ECG = electrocardiogram; TID = 3 times daily.

a Interim medical history.

b In all females. Performed in serum at Screening and in urine at all other times. A positive urine pregnancy test will be confirmed with a serum pregnancy test.

c In postmenopausal females.

d Height measured at Screening only.

e Biomarkers includes nicotinamide adenine dinucleotide (oxidized form)/nicotinamide adenine dinucleotide (reduced form), pyruvate, lactate, and other biomarkers.

f Blood for metabolomics will include a whole blood sample and a serum sample at each timepoint.

g Clinical chemistry, haematology, and urinalysis. Subjects will be fasted at least 8 hours.

h Up to 3 additional symptom-directed evaluations may be performed based on the Investigator's judgment.

i Supine and standing blood pressure and pulse rate. Blood pressure and pulse rate prior to the first dose on Day 1 will be measured in triplicate.

j Measured in triplicate.

k Performed between the Screening visit and assessments prior to the first dose.

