### **2.2. Endpoints**

#### **2.2.1. Primary Endpoints**

The primary safety endpoints for this study are as follows:

- incidence and severity of AEs
- incidence of laboratory abnormalities, based on haematology, clinical chemistry, and urinalysis test results
- 12-lead ECG parameters

- vital signs measurements
- physical examinations.

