| Clinical laboratory evaluations g                                             | X                             | X         | Day 7: Predose
Day 10: Predose and 48 hours postdose                                                                                                                                                                                            |                          | X                    | X                     |
| C-reactive protein, erythrocyte sedimentation rate, and faecal calprotectin h |                               | X         | Days 4 and 10: Predose                                                                                                                                                                                                                             |                          |                      | X                     |
| Blood pressure, pulse rate, and body temperature i                            | X                             | X         | Day 1: Predose and 2, 4, and 12 hours postdose
Days 2 to 10: Predose
Days 11 and 12                                                                                                                                                          | X                        | X                    | X                     |

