| C-reactive protein, erythrocyte sedimentation rate, and faecal calprotectin k |                                  | X         |                                         |                |          |                |                   |                |          | X g |           |    |                       |
| Blood pressure, pulse rate, and body temperature l                            | X                                | X         | Predose and 2, 4, and 10 hours postdose | X g |          | X g |                   | X g |          | X g | X         | X  | X                     |
| Safety 12-lead ECG m                                                          | X                                | X         | 2 hours postdose                        | X g |          | X g |                   | X g |          | X g | X         | X  | X                     |
| Complete physical examination                                                            | X n                   |           |                                         |                |          |                |                   |                |          |                |           | X  | X                     |
| Symptom-directed physical examination                                                    |                                  |           | X g                          | X g |          | X g |                   | X g |          | X g | X         |    |                       |
| Exit interview                                                                           |                                  |           |                                         |                |          |                |                   |                |          |                | X         | X  |                       |

Abbreviations: ECG = electrocardiogram; ET = early termination; HbA1c = glycated haemoglobin.

a Interim medical history.

b In all females. Performed in serum at Screening and in urine at all other times. A positive urine pregnancy test will be confirmed with a serum pregnancy test.

c In postmenopausal females.

d Height measured at Screening only.

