| Study residency:               |                               |                |                                                                                                                                                                                                  |                   |                      |                       |
| Check-in                              |                               | X              |                                                                                                                                                                                                  |                   |                      |                       |
| Check-out                             |                               |                | Day 12                                                                                                                                                                                           |                   |                      |                       |
| Nonresidential visit                  | X                             |                |                                                                                                                                                                                                  | X                 | X                    | X                     |
| Study drug
administration: |                               |                |                                                                                                                                                                                                  |                   |                      |                       |
| KL1333 or placebo                     |                               |                | Group D1: Days 1 to 10 (0 and 12 hours) BID with a
single dose administration on Day 10

Group D2: Days 1 to 10 (0, 8, and 16 hours) TID
with a single dose administration on Day 10 |                   |                      |                       |

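### After Day 1, no blood-pressure or pulse reading in Parts C and D is scheduled within 4 hours of a dose, so vital signs near peak are planned only after the first dose

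*Protocol*

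**What the plan says.** Section 2.2.1 lists "vital signs measurements" among the primary safety endpoints, and Section 2.1 makes multiple-dose safety and tolerability, in healthy subjects and in patients, a primary objective.

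The times are fixed in Appendix 5:

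- **Part D (Table 4).** "Day 1: Prior to first dose and 2, 4, and 12 hours post first dose"; then "Days 2 to 9: Prior to first dose"; then "Day 10: Predose Days 11 and 12"; then Days 13, 14 and 15. Dosing is "Group D1: Days 1 to 10 (0 and 12 hours) BID", and at 0, 8 and 16 h in Group D2, with a single dose on Day 10. The table notes that the "12-hour sample will be prior to second dose in Group D1".
- **Part C (Table 3).** Day 1: "Predose and 2, 4, and 10 hours postdose". Days 2, 4, 8 and 10 carry the footnote for predose. Days 11 and 15 follow.
- **Part B (Table 2).** Day 1 has readings at 2, 4 and 12 h; after that "Days 2 to 10: Predose", then Days 11 to 15.

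Section 7.3.4 allows further vital signs when clinically appropriate or when data review suggests it, without fixing a time.

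**The concern.** Readings near peak exist in the schedule only after the first dose. Readings after repeated dosing exist only near trough or during washout. The two conditions of interest in a multiple-dose safety study, accumulated drug and peak concentration, are never scheduled together for blood pressure and pulse in Parts C and D. A change that appears or grows with repeated dosing, and follows concentration within the dosing interval, could go unseen at scheduled times. The counts of subjects meeting vital-signs criteria of concern (Section 8.5) would then describe multiple dosing mainly through trough values.

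No other scheduled assessment fills the gap. Continuous ECG is confined to Parts A and B (Section 7.3.5.2). Safety ECGs in Parts C and D after Day 1 are likewise predose or on Day 11 and later, and would not give blood pressure in any case.

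**Working it through.** **1. Hours since the preceding dose, for every scheduled set after Day 1** (nominal times; early termination excluded; Day 11 taken as about 24 h after the Day 10 dose, in line with the Part C 24-h PK sample)

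| Group | Scheduled sets | Dosing-day sets (all predose) | After the final dose | Sets within 4 h of a dose |
|---|---|---|---|---|
| Part C (QD planned) | 6 (Days 2, 4, 8, 10, 11, 15) | 24 h | 24 and 120 h | 0 |
| D1 (BID) | 14 (Days 2 to 15) | 12 h | 24 to 120 h | 0 |
| D2 (TID) | 14 (Days 2 to 15) | 8 h | 24 to 120 h | 0 |

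Protocol Table 3 in Section 1.6 gives median Tmax for total KL1333 of 1 to 2 h (longest individual value 4.02 h). The finding rests on this step alone.

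**2. How far trough may lie from peak** (illustrative)

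Inputs are the mean Cmax and AUC0-∞ for total KL1333 in that same table: single doses, Korean subjects, previous assay. The protocol states no trough-to-peak figure to reproduce.

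- Average steady-state concentration: Cavg = (doses per day × AUC0-∞)/24.
- Trough cannot exceed Cavg.
- Steady-state peak is taken as single-dose Cmax plus trough. This assumes linear superposition and ignores decline of the residual before Tmax.
- Hence trough/peak is at most about Cavg/(Cmax + Cavg), and Day 10 peak/Day 1 peak is at most (Cmax + Cavg)/Cmax.

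| Regimen | Cmax (ng/mL) | Cavg (ng/mL) | Trough/peak, at most about | Day 10/Day 1 peak, up to about |
|---|---|---|---|---|
| 50 mg QD | 365.01 | 5240.32/24 = 218 | 218/583 = 37% | 583/365 = 1.6 |
| 100 mg QD | 980.18 | 10130.97/24 = 422 | 422/1402 = 30% | 1402/980 = 1.4 |
| 200 mg QD | 1385.12 | 13447.99/24 = 560 | 560/1945 = 29% | 1945/1385 = 1.4 |
| 75 mg BID (D1) | 673* | 2 × 7686*/24 = 640 | 640/1313 = 49% | 1313/673 = 2.0 |
| 50 mg TID (D2) | 365.01 | 3 × 5240.32/24 = 655 | 655/1020 = 64% | 1020/365 = 2.8 |

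*Midpoint of the 50 and 100 mg values: Cmax (365.01 + 980.18)/2 = 673; AUC (5240.32 + 10130.97)/2 = 7686.

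The Part C dose is not fixed in the protocol, so the once-daily rows are a range and not a prediction. The two right-hand columns move in opposite directions. With split dosing, trough readings sit closer to the peak, but Day 1 readings are a poorer proxy for Day 10.

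**3. The Day 1 12-h reading in Part D**

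In D1 the second dose is at 12 h, so the reading is predose, 12 h after the first dose. In D2 the second dose is at 8 h, so the reading is 12 − 8 = 4 h after it. The same nominal time therefore represents different points in the dosing interval.

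**The case against.** Several points on the other side carry weight.

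- **A reader might infer that vital signs are never measured at the steady-state peak.** The documents do not support that. Section 7.3.4 permits extra readings, an early-termination visit could fall shortly after a dose, and adverse events are collected throughout, so a symptomatic event would be recorded. What holds is that no such reading is scheduled.
- **A reader might also infer that trough readings see under a third of peak exposure.** That follows only for once-daily dosing at about 100 and 200 mg. The same bound is 37% at 50 mg once daily and 49% and 64% in the two Part D groups.
- **Comparable concentrations have been observed.** Part B reached 250 mg once daily (Section 3.4.1), with Day 1 vital signs at 2 and 4 h. Interpolating between 200 and 400 mg, single-dose Cmax at 250 mg is about 1385 + 0.25 × (2978 − 1385) = 1783 ng/mL, above the Part D Day 10 peaks of about 1020 to 1313 ng/mL. A purely concentration-driven effect at Part D levels therefore had some chance of being seen. This does not cover an effect that needs repeated dosing, nor patients in Part C.
- **There is no documented haemodynamic signal.** The dog study showed no haemodynamic change (Section 1.3), and the tolerability problem behind Part D is gastrointestinal. The endpoint promises no particular timing, so nothing in the protocol is contradicted.
- **The 12-h mismatch is minor.** Table 4 flags it for D1, and the protocol plans no D1 versus D2 comparison at that time.

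These points lower the priority. They do not change what the schedule contains.

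**Conclusion.** The gap is real but modest. In Parts C and D, a primary safety endpoint is scheduled near peak only after the first dose and, after repeated dosing, only near trough. That conclusion comes directly from the schedule and needs no pharmacokinetic assumption beyond Tmax being a few hours.

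The size is illustrative: trough at most about 29% to 37% of peak once daily, 49% for D1 and 64% for D2; Day 10 peak up to about 1.4 to 1.6, 2 and 2.8 times the Day 1 peak. These figures rest on group means from the earlier study with the previous assay, linear superposition, and interpolation for 75 mg. They show that Day 1 readings cannot be assumed to represent Day 10. They do not show that an effect exists or has been missed. The point is a cheap improvement and not a flaw that undermines the study.

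**What to change.** In Appendix 5, Tables 3 and 4, add one supine and standing blood-pressure and pulse set 2 h after the Day 10 dose. Keep the Day 10 predose set, which is that day's reference. Summarise the new set against the Day 1 2-h value within subject, by treatment.

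Subjects are on site at that time, and a 2-h PK sample is already drawn in both parts. Section 7 already places vital signs before blood draws. Section 7.3.4 requires at least 5 minutes supine and 2 standing.

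The cost is about 10 minutes for each of 8 patients and 16 healthy subjects, with no extra visit or blood, plus a small schedule amendment. With 6 active and 2 placebo per group, the result will be descriptive only.

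Part B has the same pattern but is complete. Its report should state that vital signs after Day 1 were scheduled only predose or after the final dose. The Part D report should note that the Day 1 12-h reading is predose in D1 and 4 h after the second dose in D2.
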